## Abstract

**Background:**

Asthma is a common long-term condition and major public health problem. Supported self-management for asthma that includes a written personalised asthma action plan, supported by regular professional review, reduces unscheduled consultations and improves asthma outcomes and quality of life. However, despite unequivocal inter/national guideline recommendations, supported self-management is poorly implemented in practice. The IMPlementing IMProved Asthma self-management as RouTine (IMP^2^ART) implementation strategy has been developed to address this challenge. The aim of this implementation trial is to determine whether facilitated delivery of the IMP^2^ART strategy increases the provision of asthma action plans and reduces unscheduled care in the context of routine UK primary care.

**Methods:**

IMP^2^ART is a parallel group, cluster randomised controlled hybrid II implementation trial. One hundred forty-four general practices will be randomly assigned to either the IMP^2^ART implementation strategy or control group. Following a facilitation workshop, implementation group practices will receive organisational resources to help them prioritise supported self-management (including audit and feedback; an IMP^2^ART asthma review template), training for professionals and resources to support patients to self-manage their asthma. The control group will continue with usual asthma care. The primary clinical outcome is the between-group difference in unscheduled care in the second year after randomisation (i.e. between 12 and 24 months post-randomisation) assessed from routine data. Additionally, a primary implementation outcome of asthma action plan ownership at 12 months will be assessed by questionnaire to a random sub-group of people with asthma. Secondary outcomes include the number of asthma reviews conducted, prescribing outcomes (reliever medication and oral steroids), asthma symptom control, patients’ confidence in self-management and professional support and resource use. A health economic analysis will assess cost-effectiveness, and a mixed methods process evaluation will explore implementation, fidelity and adaptation.

**Discussion:**

The evidence for supported asthma self-management is overwhelming. This study will add to the literature regarding strategies that can effectively implement supported self-management in primary care to reduce unscheduled consultations and improve asthma outcomes and quality of life.

**Trial registration:**

ISRCTN15448074. Registered on 2 December 2019.

**Supplementary Information:**

The online version contains supplementary material available at 10.1186/s13063-023-07253-9.

## Background

An estimated 3.6 million people in the United Kingdom (UK) are actively being treated for asthma [1]. Each year, asthma is responsible for over 6 million primary care consultations, nearly 100,000 hospital admissions [1] and over 1000 deaths (20 a year in children under 14 years)[2], at a cost to the NHS in England and Wales of at least £1billion [1]. Societal costs accumulate throughout life with asthma-related absence from school or work, disability and premature retirement. Much of this morbidity is preventable with appropriate/timely (self) management [3–5].

Our systematic meta-review, funded by the National Institute for Health and Care Research (NIHR) Health Service and Delivery Research (HS&DR), synthesised evidence from 27 systematic reviews (270 RCTs) and concluded that supported self-management reduces hospitalisations, accident and emergency (A&E) attendances and unscheduled consultations, and improves markers of control and quality-of-life for people with asthma [6]. A written personalised asthma action plan, completed as part of a self-management discussion and reviewed regularly, empowers patients to recognise deterioration and take appropriate action (e.g. increasing/commencing medication; seeking medical help)[7–9]. The cost of providing self-management support (estimated in a recent network meta-analysis for asthma as a 2-h investment in the first year [10]) is offset by the reduction in hospitalisations and unscheduled healthcare [6]. Effectiveness of supported self-management has been demonstrated in diverse cultural groups [11–14], children [15–17], adolescents [18, 19], adults [7] and elderly populations [20, 21], and in both primary/secondary healthcare settings [22–25]. A range of modes of delivery (including telehealth) [25–29] may be used to suit preferences and context.

For three decades [30], national and international guidelines have recommended—unequivocally—that people with asthma should be provided with self-management education, reinforced by a personalised action plan and supported by regular review with a healthcare professional [3–5]. Implementation, however, remains poor in routine clinical practice. Surveys from the UK, USA, Northern Europe and Australia reveal that less than a third of people with asthma have an action plan [31–34]. Routine primary care data from our developmental work revealed that only 6% had a record of being given an action plan [35]. In 2014, the UK National Review of Asthma Deaths highlighted that half the people who died had not accessed medical help, emphasising the vital importance of asthma self-management to facilitate timely response to deteriorating asthma control [36].

The solution will need a whole system approach [37]. An NIHR HS&DR-funded systematic review of the implementation of supported self-management concluded that whilst patient education, professional training and organisational support were all essential, they were rarely effective in isolation [38]. Effective implementation was multifaceted and multidisciplinary, engaging patients, training and motivating professionals, within the context of an organisation that actively supports self-management [39]. A systematic review of asthma implementation studies [39] identified small randomised controlled trials (RCTs) evaluating either patient education, professional training or organisational support and observational studies reporting whole system initiatives—including some very large effective national projects [40, 41]. There were no randomised trials evaluating whole system implementation strategies: a gap that the current study aims to address.

### Aims and objectives

IMP^2^ART (IMPlementing IMProved Asthma self-management as RouTine) is a UK-wide cluster randomised implementation trial that aims to test the impact of a whole system implementation strategy that embeds supported asthma self-management in primary care, compared with usual care on:Primary clinical outcome: unscheduled careImplementation outcome: ownership of an action planSecondary outcomes (Number of asthma reviews conducted, prescribing of reliever medication and oral steroids, asthma symptom control, patients’ confidence in self-management and professional support)

A health economic evaluation will assess the costs from the perspective of the healthcare service and also from a societal perspective. A process evaluation will use mixed methods to explore feasibility/acceptability of the IMP^2^ART implementation strategy and explore how supported self-management was implemented (or not) by primary care practices to aid interpretation and inform scaling up and sustainability.

## Methods

### Study design and settings

The trial uses a parallel group, hybrid II (addressing both implementation and clinical outcomes) [42] cluster randomised controlled implementation trial design (randomisation at the general practice level), testing the implementation of an evidence-based and guideline-recommended intervention. The trial will be conducted in general practices across England and Scotland. The protocol adopts the principles and terminology of the Standards for Reporting Implementation studies (StaRI) [43], uses the Template for Intervention Description and Replication (TIDieR) guide [44] to describe the implementation strategy and follows the SPIRIT checklist [45] (Additional file 1) to report the trial methodology. In addition, the CONSERVE-SPIRIT checklist [46] guides reporting of modifications due to the COVID-19 pandemic.

### Practice eligibility criteria and recruitment

We will recruit 144 general practices in the UK (England and Scotland) and randomly assign them with a 1:1 ratio to the implementation or control arm. Figure 1 shows the SPIRIT figure of the stages of enrolment, intervention and outcome assessment.

**Fig. 1 Fig1:**
[figure not shown]
SPIRIT figure of enrollment, interventions and assessments

To be eligible, practices must use one of the four common electronic health record (EHR) systems (EMIS, SystmOne, Vision or Microtest) for which components of our implementation strategy have been designed, and agree to Optimum Patient Care (OPC: a social enterprise that leads quality improvement initiatives involving routine data extraction from practices https://optimumpatientcare.org) extracting anonymised routine coded data to measure the primary and other outcomes of the study. A successful extraction of data is a requirement to (a) demonstrate that there are no insurmountable governance or technical problems, (b) establish that the practice data would allow assessment of the primary health outcome, and (c) for use in the baseline audit and feedback reports.

Practices will be of varying sizes (to reflect the range of UK primary care) and thus have different numbers of ‘active asthma’ patients. Active asthma is defined by the UK Quality and Outcome Framework (an annual reward and incentive programme for all general practices in England) as having a coded diagnosis of asthma and having been prescribed an asthma medication within the previous year [47]. Our sample size calculation takes variable cluster size into consideration, but we will exclude very small practices likely to have substantially fewer than 200 patients with ‘active asthma’ registered throughout the trial. (Note: this will be an estimate at the time of recruitment as we will not know the exact cluster sizes until the final routine data are available at the end of the trial). Finally, we will exclude practices undertaking research or initiatives that might affect our outcomes, and practices that work closely with another participating practice (e.g. as part of a network or federation). Decisions about potential contamination will be overseen by a sub-committee (chaired by [name]).

### Clinically eligible patient population

This is a practice-level intervention and we are not recruiting individual patients to the trial. Our patient population is all people who are eligible clinically to be offered supported asthma self-management by the practice. In line with national/international guideline recommendations, this is all patients with a diagnosis of ‘active’ asthma [3–5, 47]. The only exclusions (which we will apply in defining our patient populations from routine data) are:Under 5 years of age. Standard approaches to asthma self-management are ineffective in this age group [3].Under the care of a severe/difficult asthma clinic [3–5], though supporting their specialist action plan is appropriate.Significant co-morbid chronic obstructive pulmonary disease [48], as this requires a COPD action plan.Identified by the practice as being clinically unsuitable (e.g. severe cognitive impairment, on the palliative care register (a list held by the practice of those under their care who may be approaching end of life)).

Our primary health outcome (unscheduled care) will be assessed on routine data from the whole eligible population as defined above (excluding any patient whose EHR is coded as not wanting their data used for any purpose other than their care) and who have been on the ‘active asthma’ register of the practice throughout the 3-year data collection period (1-year pre-trial and 2-years during the trial).

### The IMP^2^ART implementation strategy

Informed by our understanding of the literature, and building on our developmental work [49–51], we have illustrated our ‘pathway-to-benefit’ (Fig. 2), which displays the implementation strategy. General practices randomised to the implementation group will receive the whole system implementation strategy directed at patients, professionals and the organisation, and this will be supported by expert nurse facilitation for 12 months. Table 1 displays the implementation strategy.

**Fig. 2 Fig2:**
[figure not shown]
The IMP^2^ART logic model illustrating the pathway-to-benefit

**Table 1 Tab1:** Components of the whole system IMP^2^ART implementation strategy, and adaptation for the COVID-19 pandemic

Target group	Strategy (bold is core content)	Description	COVID-19 modifications
Patient*	Asthma review invitation letters and SMS messages	Template asthma review invitation letters (including letters for annual reviews, missed review appointments, reviews following unscheduled care) that highlight the importance of reviews and asthma action plan ownership	Invitation letters adapted to include remote options, e.g. telephone/video-call
	Patient content of the *Living with Asthma* website	A range of online resources for people living with asthma (e.g. action plans, information about triggers) have been collated on patient-facing pages of the *Living with Asthma* website	Informed by a review of existing information about COVID-19 [52], tailored information about COVID-19 for those living with asthma and remote asthma review information added
	Waiting room posters	Waiting room posters for practices highlighting the importance of self-management and asthma action plans, and encouraging patients to speak to staff about these	No change
Professional**	**Module 1: Team module** [53]	A short introductory online module for the whole-practice team (e.g. administrative staff, nurses, GPs) to raise awareness of supported asthma self-management and the importance of team working. This interactive module will be introduced in the 1-h IMP^2^ART workshop, to facilitate discussion about IMP^2^ART strategies that the practice could adopt to support/embed self-management. Goals are set and summarised as the practice ‘team plan’	No change to the module, though the IMP^2^ART workshop was shifted to online
	**Module 2: Individual study **[53]	An in-depth online module for the individual(s) in the practice most involved with delivering asthma care. The module is designed for 60 min of independent study and aims to enable healthcare professionals to support effective self-management with confidence, and be motivated to adopt the IMP^2^ART resources identified in their practice’team plan’	Content was added to the module that covered effective remote consultation skills [53]
	Professional content of the *Living with Asthma* website	A range of online resources for healthcare professionals (e.g. action plans, patient information for use in reviews) have been collated on the professional pages of the *Living with Asthma* website	Added information and resources related to providing remote asthma reviews [54, 55]
Organisation***	Asthma Review Template [56, 57]	An asthma review template that will be embedded in practice systems (EMIS, SystmOne, Vision, Microtest) for use in asthma reviews. Templates will be ‘QOF-compliant’ [47], patient-centred, highlight action plan provision, and link to the *Living with Asthma* website	No change
	**Audit and feedback **[58]	Annual audit reports focusing on supported self-management will be provided at baseline, 12 and 24 months. Brief monthly reports will be delivered to practices for the duration of their participation in the trial, focusing on a summary of unscheduled care, patients reviewed and action plan provision compared to an OPC database average. The email containing the monthly report will include a ‘top tip’. Reports allow data to be de-anonymised by the practices, so that ‘at-risk’ patients can be identified and invited for review	Annual audit and feedback report updated to include a section on COVID-19: number/% of patients considered at high risk of complications due to COVID-19; number/% of patients with confirmed or suspected COVID-19; patient COVID-19 vaccination status (number/%)

^*^Developed with Patient and Public Involvement (PPI) colleagues

^**^Developed with Education for Health (EfH)

^***^Developed with Optimum Patient Care (OPC)

### Facilitation

Nurse specialists with facilitation experience will be trained to facilitate the implementation of IMP^2^ART within practices. The aim is to mimic the support that a Healthcare Trust might provide when promoting a new initiative. All implementation practices will receive an initial IMP^2^ART workshop either face-to-face or via Microsoft Teams (an approach that was added in response to COVID-19), at which the facilitator will consider the baseline audit with the practice team and introduce components of Module 1. The facilitator will guide the practice to develop their ‘team plan’ for implementing IMP^2^ART, discuss how core strategies (see Table 1) can be adopted/adapted to suit the practice routines, and identify additional strategies that might help individual practices. Facilitators will observe progress (by monitoring monthly audit reports), and offer additional support to practices struggling to implement supported self-management. Practices will receive the initial facilitated workshop and up to 10 h contact time (maximum 12 h) according to need over 12 months. A final contact at 12 months post-randomisation concludes the facilitated delivery of the implementation strategy, though all strategies (Table 1) remain available.

### Fidelity and adaptation

The core strategies will be delivered to all implementation practices including facilitation, access to Module 1, completion of Module 2 by at least one member of the clinical staff, and receipt of the audit and feedback reports. All implementation practices will be encouraged to arrange a date for the IMP^2^ART whole team workshop. If, however, a practice has not had a workshop 20 weeks post-randomisation, access to all strategies will be provided and a facilitator will offer informal support to ensure the practice is aware of all the resources. The workshop is intended to be delivered to the practice team, but if only a few members of a practice team are able to attend, arrangements for ‘cascade training’ will be discussed. Other strategies will be strongly promoted to all practices (use of the asthma review template and the patient resources), but adoption of these is optional, and practices will be encouraged to adapt the strategies to their practice routines (e.g. adding additional fields to the template to suit existing practice routines).

### Usual care in control group practices

General practices in the control arm of the trial will continue with their usual asthma care and will not receive any of the components of the implementation strategy. However, they will receive standard versions of the annual audit and feedback reports. This is an extensive report covering all aspects of asthma care that OPC routinely provide to practices contracted to their quality improvement service. In contrast to the IMP^2^ART implementation arm annual reports, there is no focus on supported self-management, and the feedback on action plan provision is towards the end of the report.

### Clinical care in both groups

Clinical care will be provided by the patients’ usual clinical advisors in accordance with the UK and/or global asthma guidelines [3–5] and according to the clinical needs of the patient.

### Adaptation of the implementation strategy in response to the COVID-19 pandemic

Although a number of practices were preparing to participate, none had been randomised when the trial was suspended in March 2020 (the start of the COVID-19 pandemic). The implementation strategy was thus not delivered pre-COVID. Between April and December 2020, we reviewed the whole IMP^2^ART implementation strategy with the help and advice of the IMP^2^ART Professional Advisory and Patient and Public Involvement Groups. The overarching strategies did not change, but we reviewed and (where necessary) adapted components to ensure they reflected the new context and the new routines in primary care (Table 1).

### Outcomes

#### Primary clinical outcome: unscheduled asthma care (second year post-randomisation)

The primary clinical outcome is the proportion of clinically eligible patients with at least one episode of unscheduled care for asthma in the second year after randomisation (supported self-management will be targeted by the implementation strategy during the first year post-randomisation, thus, impact on unscheduled care will not be apparent until the second year). Unscheduled care is defined as the proportion of people (≥ 5 years of age) with at least one unscheduled asthma consultation (GP consultation; and/or out-of-hours attendance; A&E attendance; hospital admission) during the second year in the trial (i.e. between 12 and 24 months post-randomisation). The primary clinical outcome will be measured using routine coded data extracted by OPC at 24 months from clinically eligible patients on the ‘active asthma’ register of participating practices. As there is considerable annual turnover in the ‘active asthma’ register (20% per year in one practice [59]), we will only include patients who have been on the ‘active asthma’ register of the practice at baseline, 12 months and 24 months.

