### Sample size calculations

Sample size for primary clinical outcome of unscheduled care within the previous year.

In our preliminary work, we found an unscheduled care rate of 34% [35]. We chose an absolute difference of 7% (from 34 to 27%) between trial arms as being the minimum important effect clinically and to health services. This is approximately half the effect achieved in effectiveness trials of supported self-management [6]. To detect this difference with 90% power and 5% significance level, 1868 patients would be required in an individually randomised trial without clustering.

Assuming an intraclass correlation (ICC) of 0.07 (taken from experience of pragmatic implementation studies, and supported by our analysis of data from 379 OPC practices) and assuming 200 individuals/practice, we need 70 practices (14,000 patients) in each group (increased to 72 practices/arm to allow for practice withdrawal) to detect the minimum important effect with 90% power and 5% significance level. Patients will only be included in the analysis dataset if they have ‘active asthma’ with the same practice at baseline, 12 months and 24 months follow-up, which avoids individual patient attrition. We originally intended to limit recruitment to practices with a list size > 6000 (assuming 6% will have active asthma [65]) to avoid cluster sizes < 200 (and randomly sampling if clusters were > 200). During recruitment, it became clear that this excluded many small rural general practices in Scotland, so we opted to allow variable cluster sizes (including a few clusters likely to be < 200). Furthermore, the COVID-19 pandemic resulted in a reduction in asthma attacks [66, 67], and an analysis of the OPC dataset (*n* = 286 practices) in September 2021 showed that 25.8% was a more realistic estimate of the proportion with unscheduled care that we could expect in the control group. Maintaining the recruitment target of 144 practices (140 after loss to follow-up) and allowing for a variable cluster size (mean = 200; coefficient of cluster size variation = 0.8), the study would have 94.7% power to detect a reduction from 25.8 to 18.8%.

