### Statistical analysis

Analysis will be on data at 12 months (implementation/process outcomes) and 24 months (health outcomes) follow-up. Individuals will be included in the analysis only if they were registered in a practice at baseline, 12 months and 24 months follow-up. Practices will be analysed in the group to which they were allocated regardless of compliance (intention-to-treat). The target of estimation is the average treatment effect across participants in terms of the primary clinical as well as primary implementation outcome. An unweighted independence estimating equation analysis on participant-level data will be used to estimate the participant-average difference in proportions between groups. This model employs an independence working correlation structure in conjunction with robust standard errors to account for clustering. Secondary outcomes will be analysed using the same or a similar model appropriate for the respective variable type. The models will include fixed effects for stratification variables and may incorporate additional individual-level covariates as fixed effects (covariates are limited as we are taking them from routine data). A fully pre-specified model will be provided in the statistical analysis plan (SAP). Treatment effect estimates, with associated confidence intervals and *p*-values, and ICCs will be reported for each outcome.

The primary clinical outcome as well as the secondary outcomes of unscheduled care (12 months), asthma attacks and prescribing outcomes will, by definition, not have any missing data as the absence of a code describing an event or prescription is defined as the binary variable value ‘no’. Patterns and amount of missing data for questionnaire outcomes and other routine data variables will be explored, and a suitable multiple imputation method used. The strategy for dealing with missing values will be articulated in detail in the SAP which will be prepared by the Pragmatic Clinical Trials Unit (PCTU) statisticians in consultation with other blinded research team members. Allocation codes will not be released to the statisticians before the SAP is signed off and made publicly available.

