### Strengths and limitations

A major strength of the study is the robust randomised controlled design. Additionally, the trial and the implementation components have been designed by a multidisciplinary team, including engagement with PPI colleagues and professional stakeholders currently working in primary care, strengthening the applicability to real-world practice. The extensive developmental phases have ensured that the components of the implementation strategy are theoretically based and revised after feasibility testing [28, 49–58]. However, the trial has a number of limitations; for example, late-2020 changes to the QOF to include a written personalised action plan [78] may influence English practices interest in supported self-management, though this will affect practices in both groups equally. Use of routine data allows assessment of the impact of implementing supported self-management in the population of all clinically eligible people with asthma, and our procedures for blinding of routine data extraction, handling and analysis reduce bias. Although we cannot eliminate coding discrepancies, our preliminary work has enabled us to describe the likely impact on our outcomes. Finally, although the implementation strategy was adapted for a COVID-19 context, it is uncertain what implications the pandemic may have had on the trial, although again, this will affect practices in both groups equally.

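### The primary analysis keeps only patients who still count as 'active asthma' at 12 and 24 months, which requires a prescription in each year after randomisation, so allocation can change who is analysed

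*Protocol article*

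**What the plan says.** Practice eligibility criteria and recruitment defines active asthma as "having a coded diagnosis of asthma and having been prescribed an asthma medication within the previous year".

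Four places then say who enters the analysis:

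- **Primary clinical outcome:** "we will only include patients who have been on the ‘active asthma’ register of the practice at baseline, 12 months and 24 months". The outcome is counted "during the second year in the trial (i.e. between 12 and 24 months post-randomisation").
- **Clinically eligible patient population:** patients "who have been on the ‘active asthma’ register of the practice throughout the 3-year data collection period (1-year pre-trial and 2-years during the trial").
- **Sample size calculations:** active asthma with the "same practice at baseline, 12 months and 24 months follow-up, which avoids individual patient attrition".
- **Statistical analysis:** "Individuals will be included in the analysis only if they were registered in a practice at baseline, 12 months and 24 months follow-up". This sentence does not mention active asthma.

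The Statistical analysis section applies intention-to-treat to practices. The section on the impact of COVID-19 on outcomes lists three sensitivity analyses: two forms of individual baseline adjustment and a repeated-measures model. Strengths and limitations describes the result as an "assessment of the impact of implementing supported self-management in the population of all clinically eligible people with asthma".

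**The concern.** The outcome definition and the register definition together make inclusion a post-randomisation event. Being active at 12 months needs a prescription in year 1. Being active at 24 months needs one in year 2, the same window in which unscheduled care is counted.

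The strategy works on the steps that lead to a prescription. Table 1 provides review invitations, missed-appointment letters and reports that let practices identify and invite patients. Table 2 lists reviews and prescribing as outcomes, so the trial itself allows that allocation may change them. If the strategy retains or removes patients whose risk differs from the rest, the two arms are no longer comparable, even if no attack is prevented. Keeping every practice in its allocated arm does not restore comparability among patients within practices.

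The sample size section presents the rule as a way of avoiding attrition. It does not avoid it: patients who would have been counted as lost are left out of the denominator instead.

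**Working it through.** **1. The plan's own power figure.** Inputs from Sample size calculations: 70 practices per arm after loss, mean cluster size 200, ICC 0.07, coefficient of variation 0.8, 25.8% against 18.8%.

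- Equal-cluster design effect: 1 + 199 × 0.07 = 14.93.
- Relative efficiency: 1 − 0.8² × λ(1 − λ), with λ = 200/(200 + 0.93/0.07) = 0.938, giving 0.963.
- Design effect 14.93/0.963 = 15.51; effective n = 14,000/15.51 = 903 per arm; power 94.7%, as stated.
- The design effect that matches an unweighted independence analysis is 1 + [(1 + 0.8²) × 200 − 1] × 0.07 = 23.89. Effective n is then 586 per arm and power about 82%.

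The stated arithmetic reproduces. The issue is who is analysed.

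**2. Shift in the difference when there is no true effect.** From the documents: 20% register turnover a year (one practice), so 0.8² = 64% remain after two years; control proportion 25.8%. Assumed: the strategy keeps an extra share x of the baseline register, and those patients have a 5% event proportion.

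Implementation proportion = (0.64 × 25.8% + x × 5%)/(0.64 + x).

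Null standard error with design effect 23.89: √(2 × 0.258 × 0.742 × 23.89/14,000) = 2.56 points. Type I error = Φ(−1.96 + b/SE) + Φ(−1.96 − b/SE), where b is the shift.

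| x | Implementation proportion | Shift (points) | Type I error |
|---|---|---|---|
| +0.5% | 25.64% | −0.16 | 5.05% |
| +2% | 25.17% | −0.63 | 5.7% |
| +5% | 24.29% | −1.51 | 9.1% |
| −2% | 26.47% | +0.67 | 5.8% |
| −5% | 27.56% | +1.76 | 10.6% |

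Negative x means the strategy removes such patients, for example by prompting register cleaning. With the smaller standard error implied by the stated power (2.06 points), the first three rows give 5.1%, 6.1% and 11.3%.

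**3. Which x is plausible.** The 20% turnover is not divided into patients who leave and patients who lapse. If 5–10% of the baseline register lapse and the strategy recovers 10–20% of them (both assumed), x is 0.5–2%. An x of 5% would mean recovering half to all of that pool.

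**4. Cost in power of the wider set.** Suppose lapsers are 5% or 10% of the baseline register, gain nothing and have a 0–10% event proportion. The 7-point difference becomes 7 × 0.64/0.69 = 6.5 or 7 × 0.64/0.74 = 6.1 points. With 14,000 per arm held fixed, power falls from about 94.8% (the unpooled-variance version of the 94.7%) to 92.1–92.7% or 89.0–90.5%. With the unweighted design effect it falls from 82.4% to 77.6–78.6% or 72.8–75.0%.

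**The case against.** **The mechanism is inferred.** No passage says that the strategy brings back mild patients who would otherwise lapse. The monthly reports highlight at-risk patients, adoption of the patient resources is optional, and control practices also receive annual audit reports. This stands: neither the size nor the direction can be taken from the documents. It does not remove the route by which allocation can affect inclusion.

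**An attack secures inclusion.** A reader might infer that this produces a false positive, because an unscheduled visit tends to generate a prescription while a quiet year may not. The documents do not support that. The process acts in both arms and by itself leaves a null comparison null. A between-arm bias needs the strategy to change retention.

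**Intention-to-treat.** A reader might infer that the plan breaks its own claim. It does not: the claim is worded for practices. The gap is that it gives no protection at patient level.

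**Baseline adjustment.** The planned models that adjust for each individual's baseline might absorb part of a shift towards lower-risk patients. That is fair, but no listed analysis is stated to use the wider set of baseline-active patients.

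**Leave it to the analysis plan.** Exclusion counts and supplementary sets often belong there. The primary population, however, is fixed in three sections of the protocol.

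**Registered as shorthand.** The looser sentence may be meant as an abbreviation of the active-asthma rule. As written it defines a different population, so the wording still needs aligning.

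**Conclusion.** The concern holds as a design weakness in the primary clinical analysis: inclusion depends on prescriptions after randomisation, including in the outcome year, and no listed analysis shows whether that matters.

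On the inputs above, extra retention of 0.5–2% of the baseline register shifts a null difference by about 0.2–0.6 points, against a 7-point target. Extra retention of 5% shifts it by 1.5 points. Differential removal acts in the opposite direction. These figures rest on turnover from a single practice, an assumed 5% event proportion and an assumed differential. They illustrate what could happen and do not estimate it. In particular, they do not support a reading that the trial is likely to show a spurious benefit.

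The conflict between registered and active asthma is a separate textual fact and needs correcting whatever the size of the bias.

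**What to change.** - Define the primary analysis set as patients with active asthma at baseline who remain registered with the practice through 24 months, whatever their later prescription status. Keep the always-active set as a supplementary analysis. At the least, pre-specify the baseline-active set as a sensitivity analysis of the primary clinical outcome.
- Make sure the 24-month extract retains patients who lapse. The outcome section describes extraction from patients on the register and does not confirm that lapsed patients are included.
- Tabulate by arm the baseline-active patients excluded because they left, died or had no prescription. Acknowledge that continued registration is itself a post-randomisation condition, although it does not depend on a prescription in the outcome year.
- Delete the statement in Sample size calculations that the rule avoids attrition. Use one wording in the population, outcome, sample size and analysis sections.

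The cost is mainly wording, plus a check of the extraction specification. Under the dilution assumptions above, power falls by about 2–6 points from the stated 94.7%, or by about 4–9.5 points from about 82% under the unweighted design effect.
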